# Potential Benefits

| Describe any benefits expected to result from the conduct of this study specific to a. the participant, b. the population from which the subject was drawn, and to c. society/science. Do not include compensation or incentives offered to subjects as a "benefit" to be gained from the research. Please refer to section 4.14 of the IRB Guidebook information about study benefits.  Inactivity is associated with increased disease risk and mortality. Potential immediate benefits may include increased awareness of their physical activity habits, increased knowledge of physical activity strategies for improving their physical activity habits, improved mood, energy balance, and feeling of well-being. Potential long-term benefits for participants include developing a regular physical activity routine, a potential improvement in their weight status or cardiovascular health, and reduced risk of chronic diseases.  The investigators, however, may learn more about 1) methods of increasing physical activity in overweight populations that may have public health implications for preventing disease and mortality, and 2) how to improve the use of goal setting, motivational prompts, and rewards for health behavior change. |
| --- |
| Guidance information is available in the [IRB guidebook](http://gra.sdsu.edu/irb). See the following section(s): [4.14](https://sunspot.sdsu.edu/irb/guidance.jsp?anchor=_Toc65256701) |

# Risk Assessment and Management

| 1. Description of Risks. Describe the potential or known risks associated with participation in this research. Consider and assess the physical, psychological, social, economic and/or legal harm that may result from participation in this study. Discuss whether risks would exceed those likely to be encountered by the individual in their everyday life. Assess whether the risks and inconveniences associated with the research are reasonable in relation to the anticipated benefits to the subjects and in relation to the knowledge that may reasonably be expected to result from this research.  b. Management of Risks. Describe precautions, safeguards and alternatives incorporated into the research activity to reduce or limit the severity, duration and likelihood of harm. If the study activities place the subject at greater than minimal risk for injury, describe what the potential subject will be told during the consent process and describe whether and who will cover treatment for any injury associated with the study.   c. Data Safety Monitoring Board (DSMB). When applicable, discuss the process used to monitor data collected to ensure the safety of subjects (e.g., clinical trial studies). All Phase III randomized clinical trials supported or performed by NCI require monitoring by a DSMB. For more information on DSMBs, please visit the [NCI website](http://deainfo.nci.nih.gov/grantspolicies/datasafety.htm). If this requirement does not pertain to your study, please state 'DSMB - not applicable' in the text box below. Refer to section 4.15.1 of the IRB Guidebook for guidance related to Data and Safety Monitoring Boards.   All research introduces some risk to participants. We believe that the potential risks of this study are minimal to moderate and may be psychological or physical. Participants may experience: 1) anxiety or embarrassment related to one’s personal behaviors related to physical activity habits, answering questions about one’s health or to the measurement process; 2) feelings of inadequacy or embarrassment if unable to succeed at agreed upon activity goals; 3) concern for privacy related to divulging personal information or loss of confidentiality if a computer is accessed by an unauthorized person; 4) physical injuries such as strains or sprains. Judging from our past experience and the current literature, these risks are of relatively low likelihood.   1. Risks of embarrassment or social discomfort will be minimized by fully informing participants of the topics to be discussed and the specific involvement required of them before they agree to participate. Participants will be informed that they may discontinue their involvement at any time, with no impact to the incentives previously received. Staff will be trained to provide a very positive and supportive context for the intervention and assessment. 2. The percentile intervention is designed to specifically to help participants make small, feasible changes in their activity, by prescribing goals that always fall within their previous 10 day sample of activity. These goals can both increase and decrease depending on their activity over the last 10 days. Thus, success at meeting the goals is likely for at least 30% of their attempts. 3. Participants will be told that all responses are confidential. Risks to confidentiality will be minimized by keeping screening forms, informed consent statements and participant data in separate locked file cabinets so that individuals are not easily connected to the study results. When necessary, data will be transferred from prepared forms to electronic files. Participants’ data will be stored on a password-protected computer and identifying information will not be included in the data set. Participants will be told that the SDSU Institutional Review Board will have access to research records. For individuals who do not qualify, their contact information will be destroyed 1 year after participants have been recruited into the study. All participants contact information will be destroyed 1 year after the intervention is completed. We will not re-use or disclose collected health information for other purposes. 4. Encouraging participants to be more physical active by prescribing goals might result in as strains or sprains. It should be noted that the goals participants will be provided will be equal to or less than national recommendations. ActiveReward goals are designed to both increase and decrease based on a moving assessment of their activity using the last 10 days as a window of observation. Physical activity goals for these participants will always be within the observed range of their behavior over the last 10 days. This procedure guarantees that participants will never be provided a goal outside of their abilities.   To minimize the general risk from adopting a more physical active lifestyle, we will screen for health problems with **the Physical Activity Readiness Questionnaire (PAR-Q)** during the baseline assessment. The PAR-Q has been designed to identify the adults for whom physical activity might be inappropriate or those who should have medical advice before starting an activity program. A copy of the PAR-Q has been included in this application. Additionally, we will provide all participants with **the American College of Sports Medicine and American Heart Association tip sheets** on how to minimize risk of injury while being physically active. Examples of the tip sheets have been included in this application. [name] or a research assistant will administer the PAR-Q and review these preventive tip-sheet practices with participants. All activity that participants adopt will be in their free-living environment. No activity will occur at the measurement offices. |
| --- |
| Guidance information is available in the [IRB guidebook](http://gra.sdsu.edu/irb). See the following section(s): [4.15.1](https://sunspot.sdsu.edu/irb/guidance.jsp?anchor=_Toc65256703) |

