| Address any potential problems involving subject identification, recruitment or data collection and how these problems will be resolved. Please refer to section 4.12 of the IRB Guidebook for guidance on describing potential problems in your research.  The inclusion criteria are fairly broad and inclusive. The majority of adults do not meet physical activity recommendations. Therefore, major recruitment problems are not expected. Continuous recruitment will occur for several months until 30 participants have been identified. We believe this period of recruitment is a reasonable expectation.  This study aims to help participants improve their activity using several strategies, including the requirement to self-report pedometer step counts each day. Both groups have been designed to increase physical activity and sufficiently intensive to maintain involvement. Participants will be informed at baseline that daily communication is required and should take less than 5 minutes each day. It is expected that some participants will forget to report their step counts occasionally. To plan for this possibility a pedometer with a 7-day memory display will be provided to participants so that they can still email their steps several days later. When participants forget to report their steps, they will prompted via email to report missing information during their next expected communication. Additionally, since rewards will be provided if a participant meets their daily physical activity goal, it is expected that strengthening of their reporting will also occur. These precautions should limit data collection problems.  One concern is that starting a physical activity program might result in injury. We will be screening potential participants for health problems using the PAR-Q and requiring a physician’s waiver to participate in moderate intensity physical activity intervention for those who indicate a health condition. Both interventions are designed to be equal to or less physically intense than national physical activity recommendations, which limits risk to that which would be experienced usually. We will also be advising stretching exercises to maintain a healthy body and providing stretching handout developed by the American Heart Association and the American Council on Exercise (ACE) (**both included in our application**). |
| --- |

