# Research Design and Methods

Description of Research Design

| Describe the research design, the scientific rationale underlying the proposed research and the statistical basis for the structure of the investigation. Specify aims of the research that include the hypotheses to be tested, questions to answer, data to be gathered and tested. Describe procedures used to test the hypotheses. Provide enough information about the research design to allow the IRB to make an informed judgment that the design will allow you to answer your questions and produce valid results. This information is critical to the IRB in weighing the potential benefits of the study as compared to the potential risks. Please refer to section 4.13 in the IRB Guidebook for information on IRB review of research design.  *Research Design.*  This study aims to test an adaptive goal setting intervention with frequent reinforcement (ActiveRewards intervention) to increase the number of steps/day to recommended guidelines for inactive adults by comparing to a fixed goal setting physical activity intervention. The study will be conducted with 30 participants using a two-group randomized controlled trial design with repeated pedometer measures over 6 months. The each group will experience two phases during the study consisting of a no-intervention baseline phase and one of two intervention phases. 31  *Baseline Phase.* Participants in both groups will be asked to wear a sealed Omron HJ-720ITC pedometer for the first 10 days of the study to collect baseline measures of physical activity. The pedometer will be masked with tape to obscure the number of steps taken. This will be done to reduce participant reactions to the pedometer, which will allow for a shorter baseline phase. Participants will remove the tape seal and report their steps via email after 10 days. After completing the baseline phase, participants will be randomized into either the ActiveReward or Comparison intervention groups.  The intervention components for both groups are shown in the table below. Both groups will receive similar components: 1) a pedometer, 2) self-monitoring of physical activity, 3) brief educational materials, 4) motivational prompts, 5) physical activity goals, and 6) voucher incentives.    *•• Pedometer Assessment.* Participants in both groups will be provided an Omron (HJ-720ITC) pedometer on the first day of the baseline phase, and will continue to use the pedometer throughout the entire study. The HJ-720ITC is small 1 7/8''(w) × 2 7/8''(h) × 5/8''(d) lightweight (less than 1.5 ounces) device and can be worn on a participants’ waistband or belt or kept in their pocket. The device is accurate within 3% of actual steps taken.32  *•• Self Monitoring.* Participants will use the pedometer to record the number of steps they accumulate each day. ActiveReward participants will self-report their accumulated steps to the intervention staff each day via email. It is expected to take less than 5 minutes to write an email to report each day. Comparison Group participants will report their steps weekly via email; this should take less than 20 minutes each week. We plan to make reporting easier by requiring participants to report only their ID number, the date, and steps taken. This should limit response burden.  *•• Physical Activity Education Component.* On the first intervention day, participants in both groups will be sent via email two brochures on physical activity. One was entitled, “Be Active Your Way: A Guide for Adults” published by the U.S. Health and Human Services and available at the Centers for Disease Control and Prevention website (www.cdc.gov) (Department of Health and Human Services, 2008). The publication defines physical activity and covers the national recommendations for adults. It also included a number of sections tailored to individuals’ current activity status. These sections included, “Getting Started with Physical Activity”, “Making Physical Activity Part of Your Life”, “Keeping It Up, Stepping It Up” and “Being Active for Life”. The second brochure was entitled, “100 Ways to Add 2000 Steps” by the America on the Move Foundation (www.americaonthemove.org) (America On the Move, 2008). This brochure suggests 100 ways to increase steps throughout the day with the caveat that following only one tip would not provide 2000 additional steps. Tips included “Take your dog for a walk”, “Take an aerobics step class”, “Walk around the outside aisle of the grocery store before shopping”, etc. America on the Move provides these materials free of charge to health professionals and researchers. No further educational materials will be provided to participants. Reviewing these materials is expected to take about 1 hour. The brochures are included with this IRB application.  *•• Motivational prompts.* Participants will receive motivational prompts about their physical activity to help encourage change. It is estimated that one message will be delivered every 2 weeks and participants can chose to receive these via email or text message. The prompts will include motivational messages, reminders about the health risks and benefits of physical activity, and encouraging advice developed by the PIs or research assistants. These prompts may overlap with the messages communicated in the educational component or prompt individuals to re-review the educational brochures. Both groups will receive the same prompts. Reviewing prompt messages is expected to take less than 1 minute each occurrence.  *•• Physical Activity Goals.* Both groups will receive physical activity goals, but groups will differ on the types of goal. The Comparison group will be instructed to try to meet the standard ‘usual care’ goal of at least 10,000 steps each day on at least 5 days per week. This represents a constant and fixed goal to attempt to achieve. As noted in the background selection, this goal approximates the national physical activity recommendation when activities from daily living are included in the count. This goal is commonly heard in the media and has been adopted by physical activity advocacy groups (e.g. America on the Move Foundation). Participants will receive this goal on the first intervention day and will be reminded of it periodically.  ActiveRewards group participants will be prescribed personalized, adaptive goals based on a 10-day moving sample window of their past physical activity measured by the pedometer. Participants will be informed that the goals adapt to their performance. Once a participant emails their pedometer steps, the research staff will send the next day’s step goal via email. Since the goals will adjust daily, each step goal will only good for that day. The percentile algorithm will determine new steps goals.  *•• ActiveRewards Goal Setting Algorithm.* Prior studies using pedometers and goal setting have prescribed goals for participants to meet by adding some progressive amount to participants’ baseline level or have provided a fixed goal, such as 10,000 steps per day, based on guidelines associated with national physical activity recommendations. To our knowledge, no studies to date have applied a continuously adaptive goal-setting algorithm based on participant’s own behavior.  The concept we plan to test is based on percentiles. The Percentiles algorithm requires: 1) continuous and repeated assessments of behavior, 2) rank that sample of behavior from lowest to highest, and 3) apply percentile to that distribution to determine the goal. For example, for one participant, the step count each day for the last 10 days (ranked from lowest to highest) was 1000, 1500, 2600, 4500, 5000, 5700, 6300, 6500, 8000, 11,000. This identifies the distribution of step counts. We plan to use a 70th percentile criterion with a moving 10-day window. Based on this distribution, a goal of 6,300 steps (70th percentile of the distribution) would be provided for the 11th day. Meeting or exceeding this goal would earn a reward voucher for that day. Each new day’s step count will be used to replace the oldest observation of the 10 days, re-rank the distribution, provide a new goal, and slowly but progressively increase participant’s activity behavior over time by always rewarding the top 30% of the distribution of behavior. The algorithm is adaptive, meaning that as physical activity behavior vacillates uniquely for each individual, the algorithm increases or decreases the absolute number of steps so that the goal always represents the best 30% of the last 10 days. Participants will be provided a new goal each day during the intervention phase of the study. **It is important to highlight that prescribed goals will always fall within each participant’s abilities based on a known sample of their behavior from the last 10 days. This is unlike the usual care goal of at least 10,000 steps 5 days per week, which is likely beyond their current abilities.**  One feasibility study to date tested a percentile algorithm for physical activity.33 [name] used a 40th percentile and found a 17% increase in steps/day and 32% increase in their moderate-to-vigorous physical activity minutes/day over baseline. At present, we do not know the specific percentile that will produce optimal change for physical activity behavior. Higher percentiles (e.g. 90th percentile) risk the possibility that a participant may never meet the goal since only best 10% of a participant’s behavior would meet it. As found by contingency management studies aimed at decreasing substance use, this could lead to participants experiencing frustration at the difficulty of the behavior change goals, and lead participants to drop out of the study early.34 A 5th percentile would be too easy and while this would produce consistent physical activity at some level, it would not result in longer bouts of physical activity.  *** Reward Vouchers.* ActiveReward Group participants will earn one reward point each day they reach their step goal over the 6 months. This incentive system is similar to “credit card membership reward points” that can be exchanged for various items and services. Each point will be worth $1.00. It is expected that participants will meet the programmed average of 30% of goals over the course of the intervention. This equals between $52 and $69 (+10% to be conservative) in incentives over the course of the intervention phase. Participants can bank their vouchers to save for larger payouts (e.g., $10 voucher). Participants will not earn or lose vouchers for missing a daily goal or failing to report step counts. Banked vouchers will never be subtracted. Vouchers will be sent electronically in the form of gift cards that can be exchanged after accumulating a minimum of $5 ($5 is the minimum size gift card at many companies). Electronic vouchers will be sent immediately and will be available for a select number of retailers (e.g. Apple iTunes, Amazon.com) or donation websites (e.g American Red Cross, Kiva.org). Participants in prior studies have requested an option for donation websites.  The Comparison Group will receive $70 in incentives during the intervention phase, but instead of earning for accomplishing physical activity goals, they will receive a progressively increasing amount for exchanging their pedometer each month (pedometers need to be exchanged because they only have 40 days of internal memory). Comparison group participants will a total of $70 on the following schedule: $5 for month 1, $10 for month 2, $10 for month 3, $20 for month 4, $25 for month 5. Both Groups will receive $20 for completing the 6-month questionnaire and returning the pedometer.  Finkelstein et al. found that participants who earned $7.00 for every 1% decrease in body fat lost an average 1.5% of their body weight (or 3 pounds for their 200 pound average participant) by the first opportunity earn the reward at 3 months (Finkelstein et al., 2007). In comparison, the current study offers $1.00 for each instance that participants meet their daily personalized goal which was usually less than 10,000 steps. As noted earlier, 10,000 steps/day is equivalent to 5 miles of walking. A 200 pound individual walking five miles at a moderate intensity (i.e. MET = 3.0) would take about 100 minutes and expend about 455 calories, and would earn $1.00. After matching on calorie expenditure, the current study offers an incentive about 119% more (Finkelstein et al.: 10,500 kcal = $10.50; current study: 10,500 kcal =$23.00) for the same calories expended (assuming a fixed caloric intake). However, the current study will not usually prescribe goals this difficult, so this difference could be greater. Nevertheless, compared to Finkelstein et al., the current study maximizes the fidelity of incentives by: 1) providing opportunities to earn smaller rewards more frequently (i.e. a $1 reward each day versus $7 every 3 months), 2) using a direct contingency of reinforcement for physical activity - instead of weight loss, which can include a number of desired and undesired behaviors, and 3) has a shorter latency between the occurrence of physical activity bouts and the presentation of the reward (i.e. the same day versus 3 months later for the Finkelstein et al. study).  **Statistical Considerations**  Our null hypothesis is that the ActiveRewards Intervention group will not differ in their average steps/day change compared to the Comparison intervention over the course of 6 months. The alternative hypothesis is that ActiveReward participants will show greater improvements in their physical activity change compared to the Comparison Group. Specifically, a mean difference of 1,000 steps/day between groups will be considered practically important. This effect is lower than the mean change observed by a recent systematic review of pedometer interventions but realistic given the pilot nature of the current study .26 Because this is a pilot test designed to test the feasibility of using percentiles for promoting exercise, we plan to recruit 30 participants into the study. Thirty individuals is estimated to be sufficient sample to test the concepts and determined to be financial feasible. The pilot study will test the intervention efficacy (i.e., ‘proof of concept’) and will be a preliminary study for future grants to explore this line of research.  **Data Analysis**  **Aim #1.** **To determine whether physical activity (pedometer-measured steps/day) in both the ActiveRewards and Comparison groups increased compared to their respective baseline levels.** We plan to analyze this aim using descriptive and visual methods. Means, standard deviations, and other descriptive data will be summarized by group and intervention phase. Pedometer data will be plotted on a time-series graph and phases delineated to evaluate the change in level, slope, and variability between the baseline and intervention phases of the study for all 30 participants independently and their group means. Regression models may be used to explore change by phase for each group. It is expected that each intervention phase will produce changes in the average number of steps taken per day.    **Aim #2. To evaluate whether the ActiveRewards intervention results in greater change in physical activity (steps/day) relative to the Comparison group.** Since there will be 6 months of daily pedometer data, a multi-level random-effects regression analysis will allow us to detect differences between intervention groups. The independence of observations assumption of many statistical tests are violated with time series data because repeated measures of behavior tend show serial dependence.35The multi-level random-effects analysis will allow us to use all of the available time-unstructured data from the sample of participants without imputing missing values, thus allowing for a smaller sample size. This modeling approach will also allow us to explore the autocorrelation that exists with repeated measures data.36 As noted earlier, a difference of 1000 steps/day between groups would be considered a practically important outcome. |

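### The risk section guarantees that no goal will ever exceed a participant's abilities, but the 10-day percentile rule limits goals by recent behaviour and can lag a sudden loss of ability by about a week to 10 days

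*Protocol*

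**What the plan says.** Item 4 of the risk list under Risk Assessment and Management deals with strains and sprains. It notes that ActiveRewards goals move up and down with the last 10 days and stay within the range observed over those days. It then concludes: "This procedure guarantees that participants will never be provided a goal outside of their abilities".

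The rule itself is under Research Design and Methods, ActiveRewards Goal Setting Algorithm. It is a 70th percentile on a moving 10-day window. For the ranked counts 1,000, 1,500, 2,600, 4,500, 5,000, 5,700, 6,300, 6,500, 8,000 and 11,000, "a goal of 6,300 steps (70th percentile of the distribution) would be provided for the 11th day". Each new day's "step count will be used to replace the oldest observation of the 10 days", and "the algorithm increases or decreases the absolute number of steps so that the goal always represents the best 30% of the last 10 days". On frequency: "Participants will be provided a new goal each day during the intervention phase of the study".

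The same section has a parallel but qualified sentence, in which goals stay inside each participant's "abilities based on a known sample of their behavior from the last 10 days".

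On consequences, Reward Vouchers says: "Participants will not earn or lose vouchers for missing a daily goal or failing to report step counts". At entry, Potential Problems requires a physician's "waiver to participate in moderate intensity physical activity intervention for those who indicate a health condition". The Comparison arm keeps a fixed goal of 10,000 steps on at least 5 days a week. The text at hand describes no pause of either arm's goal during an injury or illness.

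**The concern.** The premise, that goals lie within the range of the last 10 days, is true by construction. The conclusion is about what a participant can do now, and it does not follow. The two come apart when ability drops abruptly, and a sprain does exactly that. The paragraph offering the guarantee is the one meant to manage sprains.

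The ethics board is therefore told that the design has a safety property it lacks. For a week or so, a participant with a fresh injury can be sent goals built from uninjured days, with $1 attached to each. The primary comparison of steps per day is not at stake.

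**Working it through.** **Reproducing the protocol's figure.** The 7th smallest of the ten listed counts is 6,300, as stated. Interpolating definitions of the 70th percentile give 6,360 (linear), 6,400 (Hazen) or 6,440 (Weibull), so the rule in use is the 7th of 10.

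**The bound.** Let ability fall at once to a ceiling c, with every later count at or below c and one count entering the window each day. When goal k + 1 is set, the window holds k post-event and 10 − k pre-event days.
- If k ≥ 7, at least seven of the ten values are at or below c, so the 7th smallest is too.
- If k ≤ 6 and all remaining pre-event days exceed c, the goal is the (7 − k)th of the 10 − k pre-event values and lies above c.

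So k = 0 to 6 gives at most seven goals above the ceiling. If unreported days leave the window unchanged, the lag in calendar days could be longer.

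**The worked window.** The protocol lists its ten counts by rank, not by date, so every possible set of dropped days was enumerated, with post-event days at 900 steps (below the minimum of 1,000, where seven is certain):

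| Goal after event | 1 | 2 | 3 | 4 | 5 | 6 | 7 | 8 |
|---|---|---|---|---|---|---|---|---|
| Mean (steps) | 6,300 | 6,060 | 5,744 | 5,367 | 4,683 | 3,523 | 2,039 | 900 |

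Goal 7 alone ranges from 1,000 to 6,300 by day order. A ceiling between 2,000 and 6,299 steps gives one to seven goals above it. A ceiling of 6,300 or more gives none.

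**Partial drops (assumed inputs).** Daily steps were taken as lognormal with mean 5,210 (the mean of the worked window) and CV 0.30, 0.45 or 0.58 (the last is that window's sample CV). Steps fall to 20%, 40%, 55% or 70% and stay there, with 100,000 simulated participants per scenario.
- On average 6.0 to 7.0 of the first ten goals are pre-event values.
- The maximum is ten. More than seven occur in 19% of participants at CV 0.45 with a drop to 55%, and in 22% at CV 0.58 with a drop to 70%. In the first of these, 45% have at least one pre-event value among goals 8 to 10.
- Call a goal out of reach if it exceeds what the participant would now reach on 1 day in 20. Then 0.2 to 7.0 of the first seven goals are out of reach. At CV 0.45 the figures are 6.9, 5.4, 2.4 and 0.5 for drops to 20%, 40%, 55% and 70%.
- For drops to 40% or more, most pre-event values among goals 8 to 10 are within reach.
- The chance of meeting the goal is back to about 36% by goal 11 in every scenario.

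**Cost to the participant.** With stable behaviour, the chance that a new day reaches the 7th of the previous 10 is 4/11 = 36.4%.
- Over the 173 intervention days in Compensation and Incentives: 173 × 4/11 = 62.9 goals met.
- In the first ten days of a sustained event, 0.65 to 2.46 goals are met against 10 × 4/11 = 3.64, a loss of 1.2 to 3.0 goals, or about $1 to $3.
- The course total is then 59.9 to 61.7, and 59.9/173 = 34.6% to 61.7/173 = 35.7%.

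**The case against.** **Ability may mean demonstrated ability.** The sentence follows directly on the 10-day range, so the board sees the mechanism. On that reading, though, the sentence only repeats the one before it. Offered as protection against injury, it reads as a claim about present capacity. The defence does hold for the parallel sentence under Research Design and Methods, whose closing words tie ability to the 10-day sample. A reader might infer that it is equally false, but its qualifier does not support that.

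**The paragraph concerns goals that cause injury, not goals after one.** That is its opening purpose. The guarantee is nevertheless unconditional, and a pre-injury goal sent to someone with a fresh sprain is itself a goal that could aggravate it.

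**Safeguards exist.** The PAR-Q and physician's waiver act at entry. The tip sheets aim at prevention, and their full content is not shown. Participants may stop at any time, and the consent form carries a staff telephone number. Goals are sent after a step report, so not reporting works as an unofficial pause, but Potential Problems has staff prompt for missing reports. These limit the harm without making the guarantee true.

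**Stronger readings that the documents do not support.**
- That every goal in the lag is unachievable. After mild drops most remain reachable.
- That at most seven goals can ever come from pre-event days. Seven is the limit for goals above a hard ceiling. With overlapping drops, pre-event values can persist to goal 10.
- That the section's statement of likely success on at least 30% of attempts also fails. It reads as a course-level average, and one sustained event leaves it at 34.6% or more.
- That the consent form repeats the guarantee. It is not shown and is not judged here.

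**Conclusion.** The point holds and is minor. The guarantee under Risk Assessment and Management is not a property of the percentile rule. The limit of seven goals above a hard new ceiling follows from the rule alone, given a sudden, sustained loss and a count entering the window every day. How many goals are out of reach depends on the assumed variability, size of drop and 1-in-20 criterion, hence the wide range of 0.2 to 7.0 of the first seven. The documents give no injury frequency, so the number of participants affected cannot be estimated.

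Harm is limited. A missed goal forfeits only that day's $1, banked vouchers are kept, and the goal corrects itself within about 10 days. A short event costs nothing net: for a three-day event, goals met over 21 days are 7.65 to 7.76 against the usual 7.64 (21 × 4/11). The percentile design is not at fault and no analysis changes. What needs correcting is a safety statement on which the board may rely, and the lack of any described way to suspend a goal for an injured participant.

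**What to change.** 1. Under Risk Assessment and Management, replace the guarantee with: *goals always lie within the range observed in the last 10 days and may lag a sudden loss of ability by about a week to 10 days*. The parallel sentence under Research Design and Methods needs no more than alignment with this.
2. In the emails already sent to both arms, ask participants to report an injury or illness when it occurs. On a report, staff notify the investigator and pause the step goal until the participant is ready to resume. This applies to the adaptive goal and to the 10,000-step goal alike, because the fixed goal does not adapt down and a pause in one arm only would treat the arms differently.
3. State that steps are still recorded during a pause, kept in the rolling 10-day window and included in the Aim 2 analysis, so that the adaptive goal is defined on resumption and no data are lost.

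The cost is a little protocol wording and one instruction in existing emails. The downside is a few goal-free days for participants who report an event, with no $1 to earn on those days in the ActiveRewards arm.
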